## Abstract

**Background:**

Tuberculosis (TB) remains a major cause of morbidity and mortality in the world, despite being a preventable and curable disease. The World Health Organization (WHO) End-TB Strategy, aligned with the Sustainable Development Goals (SDGs), sets a target of reducing the TB mortality rate by 95%, TB incidence rate by 90%, and catastrophic costs due to TB by 2035, compared with a 2015 level. To achieve these ambitious targets, several interventions have been implemented in the last few years, resulting in major progress toward reducing the burden of TB. However, over one-third of the global TB cases remained undetected and never received treatment. Most of those undetected cases were found in low- and middle-income countries such as Ethiopia. Though several interventions were implemented to increase TB case detection and mitigate catastrophic costs associated with TB, sustaining these interventions in resource-constrained settings remains challenging. Consequently, an alternative method is needed to increase TB case detection while decreasing diagnosis delays and catastrophic costs. Therefore, this study aimed to integrate traditional TB care into modern TB care to improve TB control programs, including early TB case detection, and reduce catastrophic costs in high TB burden settings such as Ethiopia.

**Methods:**

A cluster randomized controlled trial will be conducted in northwest Ethiopia to determine the effectiveness of integrating traditional care with modern TB care. The intervention will be conducted in randomly selected districts in the South Gondar Zone. The control group will be an equal number of districts with usual care. The intervention comprised three key components, which include referral linkage from traditional to modern health care; training of health professionals and traditional care providers in three different rounds to increase their knowledge, attitude, and skills toward the referral systems; and TB screening at traditional health care sites. The primary outcomes of interest will be an increase in case detection rate, and the secondary outcomes of interest will be decreased diagnosis delays and catastrophic costs for TB patients. Data will be collected in both the intervention and control groups on the main outcome of interest and a wide range of independent variables. Generalized linear mixed models will be used to compare the outcome of interest between the trial arms, with adjustment for baseline differences.

**Discussion:**

This cluster-randomized controlled trial study will assess the effectiveness of a strategy that integrates traditional healthcare into the modern healthcare system for the control and prevention of TB in northwest Ethiopia, where nearly 90% of the population seeks care from traditional care systems. This trial will provide information on the effectiveness of traditional and modern healthcare integration to improve TB case detection, early diagnosis, and treatment, as well as reduce the catastrophic costs of TB.

**Trial registration:**

ClinicalTrials.gov NCT05236452. Registered on July 22, 2022.

**Supplementary Information:**

The online version contains supplementary material available at 10.1186/s13063-023-07559-8.

## Background

Most people with TB can fully recover from the disease with early diagnosis and treatment. However, it continues to be a leading cause of death worldwide, killing over one million people each year [1–3]. In 2020, an estimated 10 million people developed TB, and 1.4 million died as a result of TB. Of these, more than 87% of the global TB cases were reported in 30 TB high-burden countries [4]. Africa is one of the most affected regions, accounting for one-fourth (25%) of the global TB burden [5]. In Ethiopia, the incidence of TB was 140 cases per 100,000 people in 2020 [6].

The WHO has ambitious targets of a 95% reduction in TB deaths, a 90% reduction in TB incidence, and no catastrophic costs due to TB by 2035 [7]. However, according to a WHO report, approximately 4.1 million people with TB will not have been diagnosed or reported to national authorities by 2021 [8]. Most of these undetected cases were found in low- and middle-income countries or countries with weak healthcare systems. Under-detection of TB cases is also the most common problem in Ethiopia [9–11] with a high magnitude of undiagnosed smear-positive pulmonary TB (PTB) cases found in the community [12]. According to the 2021 national TB prevention and control guideline, one-third of patients with active TB remain undiagnosed and untreated in Ethiopia, and 39% of cases were not reported or not diagnosed in the Amhara region [13].

Although WHO planned to reach zero catastrophic costs, TB still causes financial hardships for the affected families [14]. Although TB medications and laboratory tests are offered free of charge in developing countries, including Ethiopia, the direct and indirect costs associated with TB are still very high [15]. TB patients face a high cost due to charges for health services in private clinics, costs for transport, accommodation, nutrition, and lost income due to the inability to work [16, 17].

Delays in the diagnosis and treatment of TB lead to slow progression of the disease, poor treatment outcomes, and an increased risk of TB transmission [18]. Delayed TB diagnosis can result in physical, social, and mental health problems such as depression, anxiety, and psychosis [19]. It can also affect social life and impose an economic burden on TB-affected families [20–22]. TB diagnosis delay in Ethiopia is unacceptable, with a previous study showing that 91% of TB patients exceeded 31 days in total delay [23]. Delays in TB diagnosis were also high in the Amhara region, with three-fifths of patients having delays in TB diagnosis and treatment [24]. The lack of appropriate intervention was the main contributor to the delay in TB diagnosis [25].

Since more people first visit traditional care, they delay visiting the modern healthcare system. Studies show that the first visit to traditional healers can lead to lower case detection, longer diagnostic delays, and higher costs. A study conducted by the WHO showed that 70–80% of the population in developing countries uses traditional medicine [26]. Traditional medicine encompasses knowledge and practices that are inherent to various cultures, whether or not they can be rationalized, and that are used to maintain health as well as to prevent, diagnose, treat, and improve physical and mental illness [27].

A recent study conducted in Ethiopia showed that more than 70% of the participants sought treatment from traditional or religious healers for a minimum of 6 months before eventually seeking care from the modern healthcare system [28]. The utilization of traditional or religious healers for an extended period before seeking modern healthcare services may have played a significant role in causing delays in diagnosing TB. Thus, integrating traditional TB care with the modern healthcare system may be important to increase case detection, reduce diagnosis delays, and reduce catastrophic costs. Integrating traditional TB care with modern care can also bridge the gap between conventional practices and contemporary medical advancements, fostering a holistic and patient-centric approach to TB management. It may also help to create a more comprehensive, accessible, and patient-friendly TB care system. Figure 1 shows the pathway and contributing factors for the low detection rate, diagnosis delay, and catastrophic cost. While the literature lacks a precise definition of “integrating traditional TB care with modern care,” for the purpose of this study, it is defined as the collaborative effort between traditional care practitioners and modern care practitioners through referral linkage and training.

**Fig. 1 Fig1:**
[figure not shown]
Conceptual framework showing the integrated systems between traditional care and modern health care system to to increase case detection rate, reduce the diagnosis and treantmet delays and catastrophic costs of TB in northwest Ethiopia

The following are the specific objectives:To determine the effect of traditional and modern care in reducing TB diagnosis delayTo estimate the effect of integrating traditional care with modern care on the cost of TB care among tuberculosis patientsTo determine the effect of integrating traditional care into modern care in increasing the TB case detection rate

## Methods and materials

This study protocol has been reported in accordance with CONSORT statement: extension to cluster randomized trials standard protocol guidelines [29].

### Study design and participants

A parallel group cluster randomized controlled trial with two arms (i.e., intervention and control arms) will be conducted in six districts of the South Gondar Zone. The outcome of interest will be case detection rate, diagnosis delay, and catastrophic costs. The control arm will include the routine standard TB cares. In the intervention arm, TB-suspected individuals (i.e., people with coughs for more than 2 weeks, fever, chills, night sweats, anorexia, weight loss, chest pain, hemoptysis, lymphadenopathy, fatigue, or growth failure in children) will be identified by the traditional healer in traditional care centers (traditional healer clinics, holy water, mosques) and referred to modern health care centers (health facilities) where there is TB diagnostic service.

### Study settings

The study will be conducted in the South Gondar Zone, Amhara regional state, northwest Ethiopia. South Gondar is one of the zones found in the Amhara region. The South Gondar Zone is bounded by East Gojam to the south, West Gojam and Bahir Dar to the southwest, Lake Tina to the west, North Gondar to the north, Wag Hemra to the northeast, North Wollo to the east, and South Wollo to the southeast. The zone covers over 14,095 km^2^ roughly. The zone has 13 rural districts, 8 town administrations (two of them have health offices), and 404 kebeles which are the lowest administrative units in the districts. According to the 2007 Ethiopia Census, the zone had a total population of 2,051,738, of whom 1,041,061 are men and 1,010,677 were women [30]. According to the zonal population projection estimate, the total population increased from 2.05 million in 2007 to approximately 2.6 million in 2020. There are more than 10 hospitals, 96 health centers, and 397 health posts. TB treatment and preventive measures are taking place in all health facilities. The direct observation therapy (DOTS) program is applied in all government health facilities.

### Interventions

The intervention comprised three key components, which include referral linkage from traditional to modern health care, training of health professionals and traditional care providers in three different rounds to increase their knowledge, attitude, and skills toward the referral systems, as well as TB screening at traditional health care sites. TB screening and diagnosis services will be done collaboratively between traditional healthcare providers and modern healthcare providers. This study defined traditional care providers as practitioners that provide informal patient care, which includes traditional healers and religious leaders. A referral linkage model will be used to detect TB cases in traditional care sites. What we add to the usual practice is screening TB-suspected patients from traditional care centers and referring them to health facilities to improve TB case detection, reduce the costs of TB, and avoid diagnosis delays. The interventions will have the following four phases.

#### Phase 1: Preliminary phase or training material preparation phase

An intervention package, including training materials, will be developed in the preliminary phases of the intervention. Experts will be invited to develop training manuals. Physicians, public health experts, and language professionals will be invited to comment on the contents, depth, readability, and understandability of the training materials. To further enrich the training manual, a workshop will be conducted, and invited experts will give their opinions. The training material will be comprehensive and comprise a domain that includes knowledge, attitude, and skill. It will contain detailed information about TB including the causes, signs, and symptoms, mode of transmission, screening and diagnosis approach, case detection methods, ways to improve treatment outcome, the benefit of early detection and treatment, complications of late diagnosis, and control and prevention mechanisms of TB. The training will also include models used to integrate traditional and modern healthcare systems. The training manual will be approved by senior experts.

#### Phase 2: Training provision

Training will be given to both traditional and modern care practitioners in three different rounds. In the first round, traditional practitioners (traditional healers and religious leaders) will be trained for 5 days. Two days of training will be given to healthcare providers (TB focal persons) in the second round, and 1-day training will be carried out in the third round at the end of the sixth month after the first round of training. The training will be given by researchers and a person having training of trainers [4] certificates at the regional health bureau. Participants that can score 75% on the post-test in the knowledge and attitude domains and are skilled in practice will be considered part of the intervention team. A pilot test will be conducted outside the study area on 5% of the project sample size based on Connelly suggestion [31]. Based on the pilot findings and experts’ judgment, the intervention package will be refined. Before the actual intervention implementation, baseline data will be collected and analyzed.

#### Phase 3: Screening and referral of TB-suspected cases

In this phase, a full-blown intervention will be implemented. Traditional healers will screen their clients for TB using standardized screening tools. All suspected TB cases at traditional healer centers, holy water, and mosques will be referred to the nearby health facilities in the intervention districts. A trained TB focal person will screen and diagnose suspected cases based on the national TB treatment guidelines. The content of the interventions, duration, frequency, and dosages are presented in table 1 in Appendix 1.

The progress and evaluation of the intervention will be assessed quarterly and at 6 months. Regular monthly supervision of the implementation will be done by assigned experts. Intermediate outcomes will be assessed during the third and sixth months of the intervention by trained assessors.

#### Phase 4: The end-line evaluation

End-line outcome assessment will be done by trained assessors. The comparison will be done between the end-line and baseline outcomes (case detection rate, cost of TB, and diagnosis delay) between the intervention and control groups.

### Randomization and recruitment

Randomization will be done at the district level. There are thirteen districts and two town administrations. Among a total of districts and town administrations, six districts and/or town administrations in South Gondar Zone will be selected using the random.org software by considering the rule of thumb assumption that covers 40% of districts and town administrations. Thus, the selected districts/town administrations will be assigned to the intervention and control arms with a 1:1 allocation ratio. This means three districts or town administrations will be randomly assigned to the intervention arm, and the other three districts or town administrations will be assigned to the control arm. District or town size will not be considered in the randomization process. All health facilities in the intervention and control arms fulfilling the eligibility criteria will be included in the study. The eligibility criteria for the inclusion and/or exclusion of health facilities will be based on the availability of TB diagnostic and treatment services, including the microscope diagnostic service and DOT programs. Participants will recruit to the study when confirmed they have any form of TB and are registered to the DOT programs. Participants will enter into the trial individually based, and patients will recruit continuously until the desired sample size achieve. Recruitment of participants will be from July 1 to September 30, 2022. The statistician who allocated the intervention and control arms, an expert who assesses the outcomes, participants who will be assigned to intervention and control arms, and healthcare providers who provide TB care will not be aware of who were assigned to the intervention and control arms. The project manager and/or investigators will be unblinded.

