### Control groups

The control sites will follow the existing passive case-finding system (self-referral patients to nearby health facilities that use the same national guidelines to treat TB). The findings obtained from the control groups will be compared with those obtained from the intervention groups. Finally, changes between the two groups will be assessed and concluded.

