### Outcomes of interest

The study will have three outcomes of interest. The primary outcome is the TB case detection rate. The secondary outcomes of interests are diagnosis delay and costs of TB care. The case detection rate will be expressed as percentage. The diagnosis delay will be defined as the time interval between the onset of symptoms and the confirmation of TB diagnosis, which includes patient delay and health system delay. The cost of TB care will include both direct and indirect costs of the patient for TB care and treatment as collected from the patients themselves and their medical records. Direct costs include out-of-pocket payments for medical services (counseling, drugs, laboratory tests, X-rays, and hospital stays) and non-medical services such as transportation, food, and accommodation costs.

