## Discussion

This cluster-randomized controlled trial will test the effectiveness of a strategy that integrates traditional healthcare into the modern healthcare system for the control and prevention of TB in northwest Ethiopia, where nearly 90% of the population seeks care from traditional care systems. Although community TB screening has been conducted by community health extension workers, traditional care centers and spiritual healing centers are not easily accessible for community screening. Thus, the integration of traditional care and modern care will be an effective intervention for improving the prevention and control of TB programs. Our study adds screening suspected patients at the place where people gather together at traditional care and holy water centers for healing. Since more than one-third of TB cases are undiagnosed in our community [13], implementing screening for suspected cases in the holy water and traditional care centers probably improves the number of missed cases in the community. In addition, TB patients are diagnosed lately after the onset of the disease and excess expenditure of household costs. This trial will provide information on the effectiveness of traditional and modern health care integration to improve TB case detection and early diagnosis and treatment as well as to reduce the catastrophic cost of TB.

This study may be difficult to reach people who are referred to a health facility by a traditional healer or religious leader for suspected TB, but who do not have a telephone and cannot go to the health facility to which they were referred for various reasons. The other limitation is the project manager and/or investigators will not be blinded.

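### Delay and cost are compared only among diagnosed patients, while the intervention changes who is diagnosed, so these two secondary comparisons are not protected by randomisation; the bias probably runs against the intervention for delay and is of uncertain direction for cost.

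*Protocol article*

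**What the plan says.** Under Randomization and recruitment, the protocol article states "Randomization will be done at the district level", with three districts or towns per arm. Individuals come in later: "Participants will recruit to the study when confirmed they have any form of TB and are registered to the DOT programs". Diagnosis delay (Outcomes of interest) runs from symptom onset to confirmed diagnosis. Catastrophic cost (Appendix 2) counts spending from symptom onset to the end of treatment against annual household income. Both therefore exist only for diagnosed patients.

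The arms differ in how patients come to be diagnosed. Control groups: "The control sites will follow the existing passive case-finding system". Interventions, in a sentence cut here before its list of aims ends: "What we add to the usual practice is screening TB-suspected patients from traditional care centers and referring them to health facilities to improve TB case". The Discussion gives the aim: "implementing screening for suspected cases in the holy water and traditional care centers probably improves the number of missed cases in the community". Detection is itself the main endpoint: "The primary outcome is the TB case detection rate".

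The Background says that going to healers first can lower detection, lengthen delay and raise cost. It cites an Ethiopian study in which "more than 70% of the participants sought treatment from traditional or religious healers for a minimum of 6 months" before reaching modern care.

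Phase 4 plans a comparison of baseline and end-line outcomes, delay and cost included, between the arms. The two sample size sections treat delay and cost as plain two-sample comparisons of proportions. Data analysis lists t-tests, logistic regression, a mixed model for cost, and covariate adjustment described for case detection.

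**The concern.** Randomising districts makes the district populations comparable in expectation. It does not make the diagnosed patients within them comparable when diagnosis is the event that the intervention is meant to increase. The intervention arm's detected group contains two kinds of patient: those who would have been diagnosed under passive finding anyway, and those found only because of the screening. The control arm has no counterpart to the second kind.

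A difference in delay or cost between the two detected groups therefore mixes two things: the effect on patients who would be diagnosed either way, and the change in who is counted. The more detection rises, the larger the second part can be. Reducing delay and reducing cost are two of the three specific objectives, and they are the only outcomes for which the article states an assumed effect and a power. A real reduction could be masked, or a change in case mix could be read as an effect.

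**Working it through.** **Plan's own figures first.** Two-sided alpha 0.05 (sidedness is not stated and is assumed), 80% power, pooled-variance formula for two proportions, then 10% added for non-response.
- Delay, 59.9% versus 45.9%: 199 per arm, 398 in total, × 1.10 = 437.8 (plan: 438).
- Cost, 40% versus 27%: 206 per arm, 412 in total, × 1.10 = 453.2 (plan: 453).

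Both reproduce, so the planned effects of 14 and 13 points are used below.

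**Inputs for the illustration**
- Baseline detection 61% = 100% − 39%, from the Amhara figure in the Background. That 39% covers cases not reported as well as cases not diagnosed, so 61% is approximate.
- Detection under the intervention 75%: assumed, because the article gives no target.
- q, the share of added cases that are delayed (or have catastrophic cost): assumed and varied, because the article gives no distribution for them.
- Patients who would be diagnosed anyway receive the full planned effect, or none.

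**Formulas**
- Share of added cases among detected patients: w = (0.75 − 0.61)/0.75 = 0.187.
- Observed intervention proportion, full effect: (1 − w) × P2 + w × q.
- Observed intervention proportion, no effect: (1 − w) × P1 + w × q.

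**Delay, full planned effect** (0.813 × 0.459 = 0.373). Power is at 199 per arm and ignores clustering.

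| q | Observed intervention proportion | Apparent benefit (points) | Power |
|---|---|---|---|
| 30% | 42.9% | 17.0 | 93% |
| 45.9% | 45.9% | 14.0 | 80% |
| 59.9% | 48.5% | 11.4 | 63% |
| 70% | 50.4% | 9.5 | 48% |
| 90% | 54.1% | 5.8 | 21% |
| 100% | 56.0% | 3.9 | 12% |

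**Delay, no effect** (0.813 × 0.599 = 0.487)
- q = 30%: 54.3%, a spurious benefit of 5.6 points.
- q = 70%: 61.8%, a spurious worsening of 1.9 points.
- q = 100%: 67.4%, a spurious worsening of 7.5 points.

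**Cost, full planned effect** (0.813 × 0.27 = 0.220)
- q = 40%: apparent benefit 10.6 points.
- q = 70%: 5.0 points.
- q = 100%: −0.6 points.

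**Cost, no effect** (0.813 × 0.40 = 0.325)
- q = 30%: a spurious benefit of 1.9 points.
- q = 70%: a spurious worsening of 5.6 points.
- q = 100%: a spurious worsening of 11.2 points.

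**Where the sign turns.** With the full effect, the benefit is understated when q exceeds P2 (45.9% for delay, 27% for cost) and overstated below it. With no effect, the turning point is P1 (59.9% and 40%).

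**A population measure for comparison.** Promptly diagnosed cases per 100 estimated cases, at q = 90%:
- Control: 61 × 0.401 = 24.5.
- Intervention, full effect: 75 × (1 − 0.541) = 34.4.
- Intervention, no effect: 75 × (1 − 0.655) = 25.9.

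Added late cases cannot lower this rate, but it rises slightly with detection alone (24.5 to 25.9).

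**The case against.** The strongest reply is that the direction is assumed. The article gives no delay or cost distribution for added cases. Appendix 1 has screening taking place daily for a year, so some cases could be caught early, and then the bias favours the intervention. The people in the cited study who spent six months or more with healers did eventually reach modern care, and the article does not say that they had TB. Patients like them may enter the control sample too, only later, and finding them sooner is a genuine gain. Part of the 39% may be diagnosed but unreported cases, who need not be long-delayed. For cost, the Background attributes spending partly to private clinics, which people still with healers may not have used; against that, Measurements counts payments to traditional practitioners.

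All of this stands as a limit on direction and size. None of it restores comparability, because the compared groups are still formed after randomisation by an event that the intervention targets.

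A reader might infer that success on detection must push both secondary outcomes the wrong way, or that the delay and cost objectives cannot be answered at all. The article supports neither: the sign depends on q, and in the delay illustration the apparent benefit ranges from 3.9 to 17.0 points.

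The remedies have limits too. A population rate mixes detection with delay. Restricting to recent symptom onset truncates long delays and still conditions on detection.

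**Conclusion.** The concern holds as a comparability problem in two secondary outcomes that the stated analysis does not handle. For delay, the article's own premises (healer-first care linked to longer delay, and screening aimed at missed cases) make bias against the intervention the more likely direction. For cost, the direction is uncertain.

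If detection rises from 61% to 75% and 60% to 100% of added cases are delayed, the planned 14-point delay benefit appears as about 11 to 4 points. These are illustrations, not estimates: the 75% and the delayed share are assumed, and 61% is read from a figure that includes unreported cases. At a 30% delayed share the comparison would overstate the benefit, and would show a spurious one if there were no true effect. This concern does not touch the primary outcome. Severity: should-fix.

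**What to change.** Keep the patient-level comparison and prespecify the following beside it.

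1. **Population-based measures by district:** promptly diagnosed cases, and cases without catastrophic cost, per 100 estimated cases or per 100,000 catchment population. If not every notified case is interviewed, apply the sampled proportion to the notified count, which requires the interviewed sample to represent the notified cases. Read the result as a joint effect on detection and on delay or cost.
2. **Results by route to diagnosis** (healer-referred versus self-presenting), with a sensitivity analysis that varies the delayed share and the catastrophic-cost share among added cases, including values below the control proportions.
3. **Optionally, an analysis of patients whose symptoms began after the intervention started**, with the same onset and diagnosis window in both arms. State that it truncates long delays and still depends on being detected.

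Also state that the comparison of all detected patients, taken alone, cannot be read as the causal effect on delay or cost.

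The cost is mainly wording and extra analysis. Delay already requires onset and diagnosis dates, and the estimated-case denominator is already used for the primary outcome. Route to diagnosis must be recorded for each patient. The main drawback is that the population measure does not isolate delay or cost from detection.

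### The protocol says TB care providers and participants are unaware of arm, but trained TB focal persons and healer-referred patients in intervention districts cannot be, and the limitations omit this.

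*Protocol article*

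**What the plan says.** Under Randomization and recruitment, the protocol article names four groups as unaware of allocation: the allocating statistician, the outcome assessor, the participants and the TB care staff. The last two are covered by one clause, which ends "healthcare providers who provide TB care will not be aware of who were assigned to the intervention and control arms". No qualification is attached. The next sentence gives the only exception: "The project manager and/or investigators will be unblinded". The Discussion carries the same single exception into the limitations: "The other limitation is the project manager and/or investigators will not be blinded".

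The Interventions section makes training of health professionals one of three intervention components, beside referral linkage and screening at traditional care sites. Under Phase 2, "Two days of training will be given to healthcare providers (TB focal persons) in the second round". Trainees who reach the post-test mark and "are skilled in practice will be considered part of the intervention team". Under Phase 3, traditional healers screen their clients and refer suspected cases to facilities in the intervention districts, where "A trained TB focal person will screen and diagnose suspected cases based on the national TB treatment guidelines". The Control groups section keeps the existing passive, self-referral system and describes no sham training or sham referral.

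**The concern.** A provider cannot deliver an intervention and be unaware of it. A patient whom a healer has screened and sent to a health facility has experienced the intervention directly. For these two groups the masking statement describes a property that the design does not have.

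This affects how results can be read. A reader who accepts the statement would take the people who report symptom onset and costs, and the person who records them, all to be masked. Diagnosis delay and patient cost would then seem better protected against differential reporting than they are. The limitations paragraph would not correct that impression, because it names only the project manager and investigators.

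Open delivery of a training-and-referral strategy is not in itself a fault. The fault lies in the description of masking and in the incomplete limitation.

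**Working it through.** The masking claim involves no figure, so the check sets the sections side by side.

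**1. TB care providers, intervention districts.** Claim: unaware. Design: trained as part of the intervention (Interventions; Phase 2), counted in the intervention team after passing (Phase 2), and diagnosing healer-referred patients (Phase 3). Appendix 1 adds a daily provider task for one year, screening patients for spiritual support. The Trial adherence section has the unblinded project manager in regular contact with TB focal persons. Result: the claim fails for trained TB focal persons.

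**2. Participants.** Claim: unaware. Under Randomization and recruitment, patients enter once TB is confirmed and they are registered for DOT.
- Healer-referred patients in intervention districts have already been screened and referred by then. They know what they received, so the claim fails for them.
- Self-referred patients in intervention districts have had no healer referral and may be unaware of the contrast.
- Control patients receive usual care and may also be unaware.

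**3. Outcome assessor.** Claim: unaware. This is feasible. It is fragile, however, because Data collection specifies a face-to-face interview that also covers health-seeking behaviour, and an answer about healer referral can reveal the arm.

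**4. Allocating statistician.** Claim: unaware. This is possible if coded units were randomized, but the text does not say how it was done.

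**5. Which outcomes are exposed.**
- Diagnosis delay (Outcomes of interest) starts at symptom onset, which depends largely on the patient's account. The text does not say that its end point, the confirmed diagnosis, is recalled.
- Cost (same section) comes partly from patients and partly from medical records.
- The case detection rate (Measurements) is notified cases over estimated cases, so it does not rest on recall.

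**6. Scale, under an assumption only.** The document gives no size or direction for any reporting difference. Suppose there is no true effect, clustering is ignored, and reporting alone lowers the intervention proportion by b points. The chance of a nominally significant result favouring the intervention is approximately

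Φ{[b√n − 1.96√(2p̄(1−p̄))] / √(p₁(1−p₁)+p₂(1−p₂))}, with p₂ = p₁ − b and p̄ the mean of the two.

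Inputs are the control proportions and per-arm sizes in Sample size determination. For delay, p₁ = 0.599, n = 208 and b = 0.05:

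(0.721 − 1.371)/0.698 = −0.93, giving 0.176.

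| Assumed b | Delay (59.9%, 208 per arm) | Catastrophic cost (40%, 214 per arm) |
|---|---|---|
| 2 points | 6% | 6% |
| 5 points | 18% | 19% |
| 10 points | 54% | 58% |

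Without any reporting difference the figure would be 2.5%. The table shows only how such a difference would act if it existed. It is no evidence that one exists, and the conclusion does not depend on it.

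**The case against.** The best defence is that randomization is by district and patients enrol only after diagnosis. Many of them (all control patients and the self-referred in intervention districts) need not know that a comparison is being made. This stands. A reader might infer that blinding of participants is impossible altogether, but the document supports that only for healer-referred patients. Even they need not know that their district was randomized, though they do know that they were screened and referred.

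A second defence reads the sentence as meaning only that staff and patients are not told about the comparison. The sentence that follows, contrasting them with unblinded managers and investigators, makes this a blinding claim, so the defence does not rescue it for trained staff.

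Three stronger readings are tempting and go too far:
- **Primary outcome biased by aware staff.** More diagnoses by trained staff are largely the effect under test. Over-diagnosis is possible, since any form of TB is eligible, but nothing in the document establishes it.
- **The statistician claim is false.** Coded units would make it true, and a condensed article may omit the procedure. It needs clarifying and is not shown to be wrong.
- **Recall-based outcomes are declared masked.** No sentence says so; it follows only from listing both informants and assessor as unaware. Nor are these outcomes pure recall: costs also use medical records.

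It is also fair to note that Data quality assurance commits to measuring outcomes the same way in both arms. That helps, but it does not remove differences in what aware patients report.

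**Conclusion.** The contradiction holds within the document. Trained TB focal persons and healer-referred patients in intervention districts are not blinded, while the Randomization and recruitment section says without qualification that TB care providers and participants are. The Discussion's limitations repeat the gap.

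The consequence is that the risk of reporting bias is understated for diagnosis delay and cost. Its size and direction cannot be derived from the document. Nothing shows that unblinding is the main source of bias in this trial, and a reader should not infer that.

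The conclusion assumes that no sham training or referral takes place in control districts, since none is described. The correction should be made: it is cheap, and it changes how both secondary outcomes can be interpreted.

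**What to change.** **Randomization and recruitment.** State that TB care providers, traditional providers and healer-referred participants are not blinded. Limit masking claims to outcome assessors and to the data analyst, who works with coded arms. Say how the allocating statistician remains unaware of the arms.

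**Discussion, limitations.** Add the lack of provider and participant blinding as a limitation for diagnosis delay and cost.

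**Data and analysis.** Use the registered date of diagnosis. If it is routinely recorded, report the bacteriologically confirmed share of notified cases by arm, as a check on diagnostic intensity.

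**Questionnaire.** Asking about referral route after symptom onset and costs would protect the assessor's masking. Make this change only if the order can be the same at baseline and end-line. Enrolment began in July 2022, data are collected at baseline and after one year, and the cost model uses change from before to after, so a mid-trial change would leave the two instruments different.

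**Cost.** A less favourable masking statement and a little extra analysis.
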